# IMPORTANCE trial: a provisional study-design of a single-center, phase II, double-blinded, placebo-controlled, randomized, 4-week study to compare the efficacy and safety of intranasal esketamine in chronic opioid refractory pain

**DOI:** 10.12688/f1000research.27809.1

**Published:** 2021-01-22

**Keywords:** Cancer pain, Esketamine, Pain measurement, Opioid refractory

## Abstract

**Background:**  Cancer is the second leading cause of death globally. Up to 86% of advanced cancer patients experience significant pain, while 10-20% live in chronic pain. Besides, increasing prescription of opioids resulted in 33,000 deaths in the US in 2015. Both reduce patients’ functional status and quality of life. While cancer survival rates are increasing, therapeutic options for chronic opioid refractory pain are still limited. Esketamine is the s-enantiomer of ketamine, with superior analgesic effect and less psychotomimetic side effects. Intranasal esketamine was approved by the FDA for treatment-resistant depression. However, its use in chronic cancer pain has never been tested. Therefore, we propose a phase II, randomized, placebo-controlled trial to evaluate the efficacy and safety of intranasal esketamine in chronic opioid refractory cancer pain.

**Methods and analysis:** We will recruit 120 subjects with chronic opioid refractory pain, defined as pain lasting more than 3 months despite optimal therapy with high dose opioids (>60 mg morphine equivalent dose/day) and optimal adjuvant therapy. Subjects will be randomized into two groups: intranasal esketamine (56mg) and placebo. Treatment will be administered twice a week for four consecutive weeks. The primary outcome is defined as reduction in the Numeric Pain Rating Scale (NPRS) after first application. Secondary outcomes include NPRS reduction after four weeks, the number of daily morphine rescue doses, functional status and satisfaction, and depression.

**Conclusion:** This study may extend therapeutic options in patients with chronic pain, thus improving their quality of life and reducing opioid use.

**Trial registration:** Clinical Trials.gov,
NCT04666623. Registered on 14 December 2020

## Introduction

Refractory pain is a challenging condition in Oncology. More than half of the patients with advanced stage cancer experienced pain
^1–
3^ and about 10 to 20% of the pain in cancer is refractory
^4^. The etiology is complex, with a mix of nociceptive, neuropathic and inflammatory mechanisms
^5^, resulting in a situation that can be difficult to control. Tolle
*et al.*, described in 2000 that around 46% of family members of terminal patients referred that there is lack of adequate pain treatment when death is imminent
^6^. When opioids are not enough to relieve pain, it is necessary to associate an adjuvant, such as ketamine, as recommended by current National Comprehensive Cancer Network guidelines in pain not responding to other analgesics
^5,
7,
8^.

Ketamine was discovered in 1980, described as a non-competitive antagonist of N-methyl-D-aspartate (NMDA) receptor causing the inhibition of excitatory glutamate receptors in the central nervous system
^5^. It is commonly used as a general anesthetic agent, administered by intravenous or intramuscular route, but other usage and routes for this drug are being studied. Ketamine can cause not only dissociative anesthesia but also an analgesic and antidepressant effect
^5^. Low doses of ketamine, have minimal effect on cardiovascular and respiratory function, produce analgesia, modulate central sensitization, hyperalgesia and opioid tolerance
^9^.

One of the ketamine enantiomers largely studied nowadays for other potential use is esketamine, the most effective optical isomer of ketamine
^3^. The advantage of this enantiomer is that it induces less dissociative effects and more powerful analgesia and anesthesia
^10^. As an antidepressant, esketamine was approved by the FDA
^10^, and as an analgesic it is not labeled yet due to the lack of studies assessing its efficacy and safety in relieving pain
^10,
11^.

Intranasal esketamine use is approved by the FDA for refractory major depression
^12^. There are a couple of recently completed or ongoing trials testing intranasal esketamine for pain
^13,
14^. A pilot study recently published found similar results in analgesia between esketamine plus midazolam via intranasal, and intravenous morphine by patient controlled analgesia in spinal surgery patients
^13^.

Esketamine has shown promising results superior to those observed for ketamine due to its more potent analgesic effect, associated with less psychomimetic side effects referred above
^15,
16^. However, a large randomized controlled trial is needed to prove that this drug is effective to relieve pain, is safe, and causes a reduction in opioid consumption. 

Finding a better approach to manage severe and refractory cancer pain through rapid and efficient analgesia would redound to the benefits of the health care of these patients. Having an alternative to escalating doses of opioid would allow a reduction in opioid consumption in this population. This would decrease the risk of overdose and the frequent and unwanted side effects associated with high doses of these drugs. Opioid consumption is an epidemic health care concern in the United States and many other countries and efforts are strongly directed to combat it
^17^.

### Objectives

This research aims to assess the efficacy and safety of a four-week treatment with intranasal esketamine (56 mg) twice a week, combined with opioid analgesic and adjuvant standard therapy in the management of adult patients with severe and opioid refractory chronic cancer pain.
****

The primary aim is to investigate the analgesic efficacy of intranasal esketamine as an add-on therapy to potentially improve opioid resistant pain in cancer patients. We will evaluate whether intranasal esketamine alleviates chronic pain in this population by assessing the reduction with the Numeric Pain Rating Scale (NPRS) after the first dose of esketamine compared to baseline
^18^.

Our secondary aims are:

1.Assessment of safety
^19^ of this novel treatment. This will be measured by a self-reported and questionnaire-guided adverse events report.2.Evaluation if esketamine treatment reduces the number of morphine rescues required daily by the patient.3.To compare the patients’ functional status between both treatment groups.4.To evaluate the response of depression score to esketamine therapy5.To analyze if there is a difference in the efficacy of esketamine depending on the type of cancer and depression disorder of the patient.6.To analyze the sustainability of the effect after each dose throughout the time of treatment.

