### Interventions

The patients will be using around the clock baseline analgesia with long-acting opioid, and morphine rescue dose for the management of breakthrough pain. In the case of neuropathic pain, patients should start the use of an antidepressant or anticonvulsant in an optimized dose. If the participant is already using any of these drugs, they should continue the medication
^1^ .

The study drug will be provided in two disposable nasal spray devices containing either 28 mg of esketamine or placebo in a 200 uL of solution - equivalent to two sprays doses. The 28 mg esketamine nasal spray device labeled “Spravato
^TM^” and a similar placebo device should be provided by the manufacturer Janssen Pharmaceutical Company of Johnson & Johnson. The participants should initially self-administer the nasal spray device containing either active drug or placebo under the supervision of a health care provider in the researcher center. Health care providers (physicians or nurses) will be informed and trained prior to the beginning of recruitment. Training will be provided by the investigators. One spray must be administered into each nostril in a 45-degree reclination to deliver 28mg. After a 5 minute interval the second device is used to deliver the second 28mg dose or placebo
^22^.

The nasal spray device contains an indicator with two green dots referring to the two spray doses. After one spray is delivered, one green dot will disappear. When the device empties after the two doses, all green dots will have disappeared. The participants will receive the intervention twice weekly for 4 consecutive weeks.

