### Outcomes

The primary outcome of this trial is a reduction in the 11-point Numeric Pain Rating Scale (NPRS). It will be used to assess pain intensity at enrollment and at each visit. Patients will be asked to rate their weekly pain on a scale from 0 to 10 where 0 equals “no pain” and 10 equals "the worst pain they can imagine”
^27^. NPRS will be taken for both during physical activity and at rest. The difference in NRPS after first dose of esketamine and baseline will be measured to analyze efficacy.

The use of a unidimensional measure is justified as the goal of this study is to evaluate the efficacy of the investigational drug as an analgesic complement for patients already consuming morphine. There are several tools to approach pain intensity and this choice (NRPS) was based on literature review on similar situations
^27–
30^.

Oncological patients suffering from chronic pain frequently present associated degrees of depression, which is why we chose a scale evaluating exclusively pain over other multidimensional questionnaires. This strategy enables to differentiate the analgesic action of esketamine from its role as antidepressant, as this itself might improve the patients’ overall well-being and disposition.

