### Sample size calculation

Sample size is based on practical and clinical considerations for this phase II trial. Based on a previous study (case series) assessing the analgesic effect of nasal esketamine
^38^ we obtained a standard deviation of 5.5 (that is the 75% upper limit of the confidence interval of the standard deviation). However, we would like to emphasize that power alone will not be relevant for the clinical interpretation of the study results, especially in a clinical trial
^39,
40^.

Considering the population of patients with refractory cancer pain (20%), to achieve a primary outcome reduction of 3 points on the 11 points NPRS with a power of 80% and an alpha error of 5%, a sample size of 108 subjects is needed. Based on previous studies in this patient population a dropout rate of 10% is estimated
^39,
41^, so for reasons of compensation, a total sample size of 120 participants will be recruited
^42,
43^.

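### The objective is four weeks of treatment, but primary efficacy is set after the first dose in three sections and over weeks 0 to 4 in a fourth, and the body names no week-4 comparison

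*Protocol article*

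**What the plan says.** The Objectives section opens with the overall aim to "assess the efficacy and safety of a four-week treatment with intranasal esketamine (56 mg) twice a week". The Interventions section confirms the schedule: "The participants will receive the intervention twice weekly for 4 consecutive weeks". That is eight dosing days.

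The primary efficacy measure is then described in four places:

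- Abstract: "The primary outcome is defined as reduction in the Numeric Pain Rating Scale (NPRS) after first application". The four-week score is ranked lower: "Secondary outcomes include NPRS reduction after four weeks".
- Objectives, primary aim: the trial will evaluate whether esketamine "alleviates chronic pain in this population by assessing the reduction with the Numeric Pain Rating Scale (NPRS) after the first dose".
- Outcomes: "The difference in NRPS after first dose of esketamine and baseline will be measured to analyze efficacy".
- Trial design: the primary endpoint is the change in NPRS at weeks 0, 1, 2, 3 and 4, with scores taken midway between doses. No deciding week, average or other summary is given.

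For the later course of pain, the sixth secondary aim in Objectives refers to how well the effect is sustained from dose to dose. The secondary outcomes refer to its pattern over the four weeks. Neither names a comparison of the arms at week 4.

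The Statistical analysis plan section allows that the effect may not persist to the next dose. In that case it offers an optional clustered analysis of acute efficacy.

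**The concern.** The objective concerns a course of treatment in patients whose pain has lasted more than three months. Three of the four statements of the primary measure concern the response to one administration. Even with a perfectly timed score, a between-arm difference after dose 1 shows that one dose lowers pain. It says nothing about whether the benefit is still there after eight doses.

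Nothing in the protocol article limits a first-dose result to a first-dose claim, and nothing makes a four-week claim depend on a four-week result. The comparison that would answer the overall objective is promised in the Abstract as a secondary outcome, but it is not carried into the body's aims or secondary outcomes as a defined contrast. The Trial design wording does reach week 4, but it conflicts with the other three sections and leaves the deciding time point open. A short-lived effect could therefore be reported as success for a four-week treatment of chronic pain.

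**Working it through.** **Inputs.** From Sample size calculation: difference 3 NPRS points, SD 5.5, power 80%, alpha 5%, 108 evaluable, and "a dropout rate of 10% is estimated". From Statistical analysis plan: two-sided tests. From the Abstract: two groups. The allocation ratio is not stated, so 1:1 is assumed.

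**Step 1: reproduce the plan's sample size.**

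- Normal approximation, per arm: n = 2 × (1.96 + 0.84)² × (5.5/3)² ≈ 2 × 7.85 × 3.36 ≈ 52.8, so 53 per arm and 106 in total.
- Two-sample t-test: 53.74, so 54 per arm and 108 in total. This matches the plan.
- Dropout: 108 / 0.9 = 120. This also matches.

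**Step 2: chance of a positive first-dose test when the effect does not last.** Suppose the true difference is 3 points after dose 1 and 0 at week 4. The first-dose test depends only on the first-dose difference, so its chance of success is its ordinary power.

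- 54 per arm: standard error 5.5 × √(2/54) ≈ 1.058; 3 / 1.058 ≈ 2.83; t-test power 80.2%.
- 60 per arm, if nobody is lost before the first-dose score: t-test power 84.2%.

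**Step 3: the same trial judged at week 4.** Simulation with 54 per arm, SD 5.5 at both times, and 20,000 runs at each within-patient correlation of 0, 0.3, 0.5 and 0.7:

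| Rule | Trials meeting the rule |
|---|---|
| First-dose test significant | 80.0% to 80.7% |
| Week-4 test significant | 4.9% to 5.1% |
| Both significant | 2.9% to 4.1% |

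In this scenario, the choice of time point alone moves the chance of a positive result from about 80% to about 5%.

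**Step 4: does a week-4 comparison need more patients?** On the same inputs, no. 120 × (1 − 0.10) = 108 evaluable, which gives 80.2% power. This assumes that the 3-point difference and SD of 5.5 also hold at week 4. The Sample size calculation section ties neither figure to a time point.

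**The case against.** An acute primary endpoint is a legitimate choice in phase II, and the Abstract discloses it openly. The sentence labelled as the primary aim speaks of analgesic efficacy as add-on therapy and does not mention four weeks. The four-week wording belongs to the umbrella statement on efficacy and safety together. The introduction stresses rapid analgesia. The figure of about 80% is simply the trial's power for its stated effect, and the zero effect at week 4 is hypothetical. NPRS is recorded at every visit, and all primary and secondary analyses are said to compare the two arms, so some between-arm look at pain over the four weeks is planned. No sentence says that a first-dose win will be reported as four-week efficacy.

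Much of this stands. The first-dose primary need not be abandoned, the 80% shows exposure rather than an arithmetical error, and the over-claim is a possibility rather than a stated intention. The objection does not remove the mismatch. The same section that sets a four-week objective says relief of chronic pain will be evaluated after the first dose, and no text limits what that result may be used to claim.

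A reader might go further and infer that efficacy is judged by the first dose alone, that a trial without four-week benefit would necessarily be declared positive, or that a four-week score appears only in the Abstract. The documents do not support these readings. Trial design names change through week 4 as the primary endpoint, so if that section governs, the consequence does not follow automatically. The secondary outcomes explicitly cover the effect over the four weeks.

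**Conclusion.** The point holds in a limited form. The four-week objective does not match the first-dose measure given in the Abstract, Objectives and Outcomes, and Trial design gives a different primary endpoint without a deciding week or summary. If the first-dose definition applies, a trial with a 3-point first-dose effect and no week-4 effect could be positive with about 80% probability (84% if all 120 are evaluable at that time). A test at week 4 would be positive in about 5%.

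These figures rest on the plan's difference, SD and two-sided 5% level, on 1:1 allocation, and on a hypothetical effect that has vanished by week 4. The planned 108 and 120 reproduce and are not in question. What is affected is the conclusion the trial can support, so the text should be corrected before recruitment starts.

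**What to change.** 1. Reconcile the Abstract, Objectives, Trial design and Outcomes to one primary endpoint and one time point. If the Trial design endpoint is the intended one, state which week or which summary of the weekly scores decides.
2. If the first-dose primary is kept, state in Objectives and Outcomes that it supports only a claim of analgesia after a first dose.
3. Add the between-arm difference in NPRS at week 4 to the aims and the secondary outcomes as the named key secondary outcome, tested only if the primary is significant. This fixed order holds the overall error rate for the two tests at 5%. In the scenario above, a four-week claim would then be made in about 3% to 4% of trials.
4. Make any statement of four-week or chronic-pain efficacy conditional on that week-4 result.

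The change is to wording and test order. It uses scores already scheduled and, if the plan's difference and SD apply at week 4, no more patients. The study is not yet recruiting, so the cost is low. The one drawback is that a win on the first dose alone supports a narrower headline claim.

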### Trial design

We propose a single-center, randomized, placebo-controlled, phase II, double-blinded with two parallel groups, superiority trial. The primary endpoint will be the change in pain intensity measured by the NPRS
^18^ (at week 0, 1, 2, 3, and 4, measured exactly in between doses).

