***Secondary outcomes.***
* Sustainability of effect.* NRPS will be used to identify the pattern of effect after each dose over the 4 weeks.

*Rescue morphine use*. The use of morphine rescue (whether it will be reduced, no change, or increased). If pain decreases or stabilizes during the trial. This will be monitored using either the Aircure artificial intelligence through a mobile application or personal diaries.

*Patients’ functional status and satisfaction.* These will be measured by the change in Brief Pain Inventory (BPI). A multidimensional standardized tool as the BPI will allow the researchers to assess pain intensity in relation to its interference in functional activities
^31^.

*Depression symptoms.* Depression is frequently described in association with chronic pain and affects its threshold. On the other hand, esketamine has a proven antidepressive effect. We propose to examine a depression score using the Patient Health Questionnaire (PHQ9) at enrollment and at each visit
^32^. We would also evaluate the effect of depression on the analgesic effect of esketamine.

*Side effects.* Reported side effects in other studies include decline in mood, conscious perceptions and intellectual performance. It is well established that esketamine presents fewer side effects than the racemic ketamine
^33^. In this protocol the dissociative effects of the drug will be monitored applying the Side Effect Rating Scale for Dissociative Anesthetics (SERSDA) at enrollment and at each visit
^34^. It assesses fatigue, dizziness, headache, nausea, changes in vision and mood changes. The cognitive performance will be addressed using Speed Reading Test (where the time for reading 20 independent characters is noted)
^33^.

*Vital signs.* Blood pressure, heart rate, respiratory rate and temperature, pulse oximetry and 12-lead-ECGs will be measured at enrollment and at each visit (prior, 40 minutes and 2 hours after intranasal application of the drug or placebo). In the occurrence of any abnormality, patients will be advised to stay at the institution for complementary evaluation. Furthermore, lower urinary tract symptoms will be asked and in case of positive answers, further examination will be performed
^35^.

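### The primary endpoint is defined inconsistently (NPRS change after the first dose, or at weeks 0 to 4 between doses), and a weekly-pain rating does not fit the first-dose definition

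*Protocol article*

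**What the plan says.** Three sections tie the primary endpoint to the first dose. The Abstract states: "The primary outcome is defined as reduction in the Numeric Pain Rating Scale (NPRS) after first application". Objectives describes the reduction as that seen "after the first dose of esketamine compared to baseline". Outcomes says that efficacy will be analysed from the difference between the score after the first dose and baseline. None of them gives an hour or day for the post-dose score.

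Trial design names the NPRS change as the primary endpoint but attaches a different schedule: "at week 0, 1, 2, 3, and 4, measured exactly in between doses".

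Later scores are placed among the secondary outcomes. The Abstract says "Secondary outcomes include NPRS reduction after four weeks", and Secondary outcomes says "NRPS will be used to identify the pattern of effect after each dose over the 4 weeks".

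On measurement, Outcomes says of the NPRS: "It will be used to assess pain intensity at enrollment and at each visit". On recall it says: "Patients will be asked to rate their weekly pain on a scale from 0 to 10". It adds: "NPRS will be taken for both during physical activity and at rest". Neither condition is named as primary.

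Three other statements bear on this. Interventions sets dosing at twice weekly for four weeks, and Blinding places administration at the facility. Secondary outcomes fixes post-dose clock times (40 minutes and 2 hours) for vital signs and ECG, and no section fixes one for the NPRS. The Statistical analysis plan section allows that the effect may wear off before the next dose.

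**The concern.** A single-dose change and a series over weeks 0 to 4 answer different questions: whether one application relieves pain, and whether relief is sustained under repeated dosing. The trial has one 5% alpha and one power statement. If both definitions stay in the protocol, the choice between them could be made after the data are seen. The unresolved choice between rest and activity doubles the candidates.

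The recall period is a second problem, and it would remain if everyone agreed on the first-dose definition. A rating of the past week mixes pain from before dose 1, or pain after dose 2, into a score meant to describe dose 1. An effective drug could then look weaker than it is on the endpoint for which the trial is powered.

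**Working it through.** **1. Which variable is primary?**

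| Section | Primary variable or timing | Status of later weeks |
|---|---|---|
| Abstract | Change after first application | Four-week change is secondary |
| Objectives | Change after first dose versus baseline | Sustained effect is a secondary aim |
| Trial design | Change at weeks 0, 1, 2, 3, 4, between doses | Part of the primary endpoint |
| Outcomes | Change after first dose versus baseline; scores at enrollment and each visit | Not stated |
| Secondary outcomes | – | Pattern after each dose is secondary |

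Weeks 1 to 4 are therefore primary in one section and secondary in two others. The timing conflicts too: dosing takes place at facility visits, so a score taken at a dosing visit is not midway between doses.

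**2. Which definition does the sample size fit?** Inputs from Sample size calculation: difference 3 points, SD 5.5, power 80%, alpha 5%, dropout 10%. The tests are two-sided (Statistical analysis plan section). Equal allocation is assumed because no ratio is stated.

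- Normal approximation: n per arm = 2 × (1.960 + 0.842)² × 5.5² / 3² = 2 × 7.85 × 30.25 / 9 = 52.8, so 53 per arm and 106 in total.
- Two-sample t-test: 53.74, so 54 per arm and 108 in total, which is the protocol's figure.
- Dropout: 108 / (1 − 0.10) = 120, also the protocol's figure.

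The stated size is reproduced by one comparison of one value per patient. That fits a single first-dose change and not a five-time-point endpoint.

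**3. Can a weekly rating isolate dose 1?** Two doses a week, evenly spaced, are 7 / 2 = 3.5 days apart (assumption; the documents give no spacing).

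- Rating made before dose 2: at most 3.5 of the 7 recalled days follow dose 1, and the rest precede it.
- Rating made later: the recalled week includes time after dose 2.

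Neither describes dose 1 alone. Randomization implies that pre-dose pain does not differ by arm in expectation, so the pre-dose days contribute no difference and pull the contrast towards zero.

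**4. Illustration of size.** Further assumptions: recall is an even time average, the 3-point effect is constant until dose 2, and the SD stays at 5.5 with 54 per arm.

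- Diluted effect = 3 × 3.5 / 7 = 1.5 points.
- Standard error = 5.5 × √(2/54) = 1.058.
- Power for 3 points = Φ(3/1.058 − 1.960) = Φ(0.87) = 81% (t-test 80.2%).
- Power for 1.5 points = Φ(1.5/1.058 − 1.960) = Φ(−0.54) = 29% (t-test 29.0%).

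Across a range of assumed diluted effects, the same formula gives 47% at 2 points and about 16% at 1 point.

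**The case against.** The weight of the text favours the first dose: three sections agree, and the four-week results are called secondary. The parenthesis in Trial design is the outlier and may have been meant as an assessment schedule with week 0 as baseline. This stands in part. It shows which definition to keep and makes a choice after the fact less likely. It does not remove the conflict, because the parenthesis qualifies the primary endpoint itself and its timing disagrees with Outcomes.

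A reader might infer that the first-dose effect cannot be measured at all. The documents do not support that. A current-pain score between doses 1 and 2 would measure it, and the timeline figure, which may show the collection points, is not available here. The problem is that the text asks for weekly pain and fixes no such score.

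A reader might also infer that five weekly readings cannot show the pattern after each of eight doses (2 × 4). That follows only from the Trial design schedule. Outcomes takes the NPRS at every visit, which could supply more readings, so the disagreement between the two schedules is the real issue.

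Finally, the dilution figures rest on assumptions that the documents do not contain, and the protocol sets its 3 points on the primary outcome as measured. A constant effect until dose 2 also sits awkwardly with the protocol's own allowance that the effect may fade. This stands, and it is why the figures are only an illustration.

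**Conclusion.** The concern holds as an inconsistency in the current text and should be resolved before recruitment, which has not begun. Two definitions of the primary endpoint coexist, the later weeks are both primary and secondary, the two NPRS schedules disagree, and neither rest nor activity is named as primary. Separately, weekly recall does not fit a first-dose endpoint under twice-weekly dosing. Its pre-dose days bias the effect towards zero, and waiting longer brings in dose 2.

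The direction of the bias follows from randomization, but its size is unknown. The drop from 80% to about 29% power holds only under the four conditions given in the working (3.5-day spacing, even recall, constant 3-point effect, unchanged SD with 54 per arm). It should not be read as the power the trial will have. A weekly rating taken within hours of dose 1 would be diluted far more, but no section schedules one. The sample-size arithmetic is not in error on this point.

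**What to change.** Reconcile the Abstract, Objectives, Trial design and Outcomes to one primary variable. Keep the first-dose endpoint, since it is the majority text and matches the single-comparison sample size. Define it as:

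- current pain on the NPRS, not weekly pain;
- under one named condition, rest or activity;
- at one fixed time after dose 1 and before dose 2, minus the same score just before dose 1;
- compared between esketamine and placebo.

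The sponsor should choose the time before recruitment. The 40-minute or 2-hour points already used for vital signs are one option, and a reading just before dose 2 is another. An early self-report may be more exposed to unblinding through dissociative effects. A reading just before dose 2 asks whether relief lasts that long, which the protocol itself treats as uncertain.

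Record rescue use between the two readings. Make the weekly and week-4 scores secondary throughout. Take the same post-dose reading at each dosing visit, so that the secondary aim on sustained effect after each dose can be answered.

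The cost is small: protocol wording and about one extra NPRS line per dosing visit, when patients are already on site.
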